### Study Objectives and Endpoints

2.3

The primary endpoint of the MICO study will be to evaluate the concordance between in vitro platinum‐based chemotherapy sensitivity and in vivo sensitivity.

In more detail:
Organoids generation in vitro system to evaluate tumoral cells' response to carboplatin treatment.Patient's clinical response monitoring. We will record platinum‐free interval (defined as interval expressed in months between the last dose of platinum‐based chemotherapy and the recurrence or progression of the disease), progression‐free survival (calculated from the first surgery until the first disease progression or the last follow‐up) and overall survival (defined as the length of time from the date of first surgery to death or the date last seen). The disease recurrence or progression will be evaluated according to RECIST1.1 [32]. Relapsed patients will be divided according to response to platinum treatment as resistant (platinum‐free interval 1–6 months of last platinum cycle) and partially platinum‐sensitive/platinum‐sensitive (platinum‐free interval > 12 months).

The model will be considered concordant if PDOs of platinum‐resistant patients will be viable on day 5 after carboplatin addition and if PDOs of platinum‐sensitive/partially platinum‐sensitive patients will not be viable (see Section 2.8).

The secondary endpoints will be:
Characterize the composition of the immune TME in order to understand if there are differences between tumor‐infiltrating immune subpopulations among patients, differences that could be predictive of early recurrence and/or different responses to therapy, focusing on immune populations still poorly studied (such as B cells for acquired immunity and mast cells for innate immunity).Organoids generation in vitro system to evaluate tumoral cells' viability in response to PARP‐I treatment.Association of TME composition, organoid response to drugs, and clinical evidence to identify predictors of response to therapy.To compare the TME of HGSOC patients with the TME of the control group.To develop a platform that allows in vitro analysis of the tumor followed by the identification of personalized therapy for each patient and, in case of recurrence, to monitor over time changes in the composition and responsiveness of the patient's TME.

As exploratory endpoints, immune cells from patients that have responded to platinum therapy and from patients that have relapsed within 18 months would be investigated at a single‐cell level throughout single‐cell RNA‐seq and CITE‐seq approaches, multi‐omics techniques for obtaining transcriptome and surface‐proteome information, respectively, at a single‐cell level. This will help in the identification of altered molecular pathways in B cells, mast cells, and other cells of interest in the TME, to possibly discover novel therapeutical targets.

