### Sample Size

2.4

The sample size was calculated in order to evaluate the concordance between in vitro platinum‐based chemotherapy sensitivity and in vivo sensitivity.

From literature, this concordance is 0.80 with traditional patient‐derived xenografts [33]; we expect a concordance of 0.95 using PDOs [34]. A sample size of 93 patients will allow us to detect a true value of Cohen's Kappa of 0.95, with a power of 80% and an allocation of the two groups of 1:1.

Ninety‐three control patients will also be enrolled to compare the number of CD45+ cells at baseline. This sample size will allow estimating an effect size of CD45+ cell number of less than 0.3 between the control and case groups, with an alpha of 5% and power of 80%.

[32, 33].

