### Statistical Methods

2.11

The sample will be described in its characteristics using descriptive statistical techniques. Quantitative variables will be summarized with mean, standard deviation, minimum, and maximum. Qualitative variables will be described with frequency tables (absolute and percentages).

We will record platinum‐free interval, progression‐free survival, overall survival, and sensitivity to platinum‐based chemotherapy.

A univariate and multivariate Cox analysis will be implemented to explore factors associated with progression‐free survival. The proportional hazard assumption will be tested using the Schoenfeld residual test. Multivariable analysis will be corrected for potential confounding factors. Survival curves will be obtained using Kaplan–Meier analysis. All statistical tests will use a two‐tailed significance level of 0.05. The *χ*
^2^ test or Fisher's exact test will be used to analyze the distribution of variables according to different subgroups. The non‐parametric Wilcoxon test will be used to analyze the distribution of continuous variables.

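### Progression-free survival is defined without death as an event, so the endpoint analysed is time to progression, and Kaplan–Meier estimates labelled PFS are overstated if patients die without documented progression

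*Protocol article*

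**What the plan says.** Section 2.3 (Study Objectives and Endpoints) defines the clinical outcomes in one sentence. PFS is "calculated from the first surgery until the first disease progression or the last" follow-up. Overall survival is "defined as the length of time from the date of first surgery to death or the date last seen". The next sentence says how progression is judged: "The disease recurrence or progression will be evaluated according to RECIST1.1". No section makes death a PFS event.

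Section 2.11 (Statistical Methods) then uses the endpoint: "A univariate and multivariate Cox analysis will be implemented to explore factors associated with" progression-free survival. It adds: "Survival curves will be obtained using Kaplan"–Meier analysis. It names no competing-risk method.

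**The concern.** PFS is meant to be a composite: alive and without progression. The definition gives two ways for a patient's time to end, progression or last follow-up. Someone who dies before progression is documented fits only the second and leaves the analysis as censored. The patient is then treated as if progression could still occur later, when in fact the patient has died.

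Such deaths are plausible in this study. Patients have FIGO stage III–IV disease and may be up to 80 years old (Table 1). The clock starts at first surgery, so deaths after the operation or during neoadjuvant chemotherapy fall inside the window. The follow-up visits in Section 2.1 are six months apart, and 12 months apart between month 24 and month 36, so a patient could progress and die between visits with no RECIST record.

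At stake are the Kaplan–Meier curve, its median and its landmark percentages, which would be read as PFS, and the meaning of the hazard ratios from the Cox models.

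**Working it through.** **1. The plan's own figure.** The article states no PFS median, event count, hazard ratio or power, so no PFS figure can be reproduced. The only sizing tied to the primary endpoint is 93 patients for a kappa of 0.95 against 0.80, "with a power of 80% and an allocation of the two groups of 1:1". With 50% prevalence the variance of kappa is (1 − κ²)/n. At two-sided 0.05:

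n = [(1.960 × √(1 − 0.80²) + 0.842 × √(1 − 0.95²)) / (0.95 − 0.80)]² = [(1.960 × 0.600 + 0.842 × 0.312) / 0.15]² = 92.003, rounded up to 93.

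The stated figure reproduces. PFS does not enter it, so redefining PFS leaves it unchanged.

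**2. Direction of the Kaplan–Meier error.** Take the same patients at risk at each time. Censoring a death instead of counting it removes an event and leaves the risk set as it was. Each step of the curve is then the same or smaller, so the curve as defined is never below the PFS curve. It is higher as soon as one such death occurs.

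**3. Size of the Kaplan–Meier error.** Both inputs are assumptions, because the article gives neither:
- true median PFS of 16 months, with constant hazards;
- f, the share of first events that are deaths without documented progression.

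The total hazard is ln 2 / 16. The progression-only hazard is (1 − f) times that. So the reported median is 16 / (1 − f), and reported 12-month PFS is 0.5 raised to the power (12/16) × (1 − f). True 12-month PFS is 0.5^0.75 = 59.5%.

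| f | Reported median (true 16.0 months) | Reported 12-month PFS (true 59.5%) |
|---|---|---|
| 2% | 16 / 0.98 = 16.3 | 60.1% |
| 5% | 16 / 0.95 = 16.8 | 61.0% |
| 10% | 16 / 0.90 = 17.8 | 62.6% |
| 15% | 16 / 0.85 = 18.8 | 64.3% |

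The relative error in the median, 1/(1 − f), does not depend on the assumed 16 months. Starting instead from a reported median of 18.0 months, counting death gives 17.6, 17.1 and 16.2 months at f = 2%, 5% and 10%.

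**4. Effect on the Cox models.** With deaths censored, the model estimates the cause-specific hazard ratio for progression, HR_prog. Under constant hazards, with f the share in the reference group, the PFS hazard ratio is (1 − f) × HR_prog + f × HR_death. Take HR_prog = 1.5 and f = 10%; both are assumed:
- HR_death = 3: 0.9 × 1.5 + 0.1 × 3 = 1.65, so the fitted 1.50 is below the PFS value.
- HR_death = 1.5: 0.9 × 1.5 + 0.1 × 1.5 = 1.50, no difference.
- HR_death = 1: 0.9 × 1.5 + 0.1 × 1 = 1.45, so the fitted 1.50 is above the PFS value.

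The gap can go either way, and it vanishes when a factor acts equally on both events.

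**The case against.** The strongest reply has four parts.

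- **The article is condensed.** The definition gives a time span and does not use the word censored; a fuller document may code the events properly. This carries little weight. The overall survival definition in the same sentence names death, so the authors listed it where they meant it. A plan that counted deaths in PFS would contradict the published definition.
- **The Cox model is not wrong in itself.** A progression-specific hazard ratio is a legitimate quantity. For the secondary aim about early recurrence it may even be the closer target. This stands. A reader might infer that the Cox results are biased across the board, that factors which raise early death will always look less harmful, or that the choice of predictive immune populations is distorted. The documents do not support this: Section 2.11 lists no covariates, nothing is said about how any factor acts on death without progression, and step 4 shows that the direction is not fixed.
- **The sizes are assumed.** This also stands. At a 2% share the median moves by about 0.3 months and 12-month PFS by under one percentage point. If nearly all deaths follow documented progression, the numerical effect is small.
- **Little depends on PFS.** It does not decide the primary endpoint or the sample size, and its Cox analysis is described as exploratory. This stands and limits the weight of the point, but it is no reason to leave the endpoint mislabelled.

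**Conclusion.** The point holds as one of definition. As written, the endpoint is time to progression with deaths censored, not PFS, and a Kaplan–Meier curve presented as PFS is too high whenever a patient dies without documented progression. With an assumed true median of 16 months and 2% to 15% of first events being such deaths, the reported median is about 16.3 to 18.8 months, an overstatement of 2% to 18%. The article gives no data to place the study within that range, and the true share could be lower.

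For the Cox models the conclusion is narrower: they answer a question about progression, and they differ from PFS hazard ratios only for factors that act differently on death. The concordance endpoint and the 93 patients are untouched.

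**What to change.** Change one sentence in Section 2.3. Define PFS as the time from first surgery to first progression by RECIST 1.1 or death from any cause, whichever comes first. Censor patients who are alive and progression-free at last follow-up or last disease assessment, and state which.

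If only progression is of interest, rename the endpoint time to progression in Sections 2.3 and 2.11 and treat death as a competing event. In that case report the cumulative incidence of progression in place of one minus Kaplan–Meier, and describe the Cox results as progression-specific hazard ratios.

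The cost is negligible. Deaths are already recorded for overall survival, so no new data and no change in sample size are needed. The change is best made before outcomes are examined.

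### The platinum-response classes behind the primary concordance endpoint are not exhaustive and do not match their own label, so the endpoint is undefined for part of the 93 patients on whom the power rests

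*Protocol article*

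**What the plan says.** Section 2.3 (Study Objectives and Endpoints) makes agreement between in vitro and in vivo platinum sensitivity the primary endpoint. The first in vivo class is set out as follows: "Relapsed patients will be divided according to response to platinum treatment as resistant (platinum‐free interval 1–6 months of last platinum cycle"). The other class has a double label with a single cut-off: "partially platinum‐sensitive/platinum‐sensitive (platinum‐free interval > 12 months").

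The platinum-free interval is the "interval expressed in months between the last dose of platinum‐based chemotherapy and the recurrence or progression of the disease". It has no end date for a patient without an event. Progression-free and overall survival, defined alongside it, do run to last follow-up or the date last seen.

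The agreement rule is written for the two named classes only. It begins "The model will be considered concordant if PDOs of platinum‐resistant patients will be viable on day 5 after carboplatin addition" and goes on to require non-viable organoids in the sensitive or partially sensitive class.

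Section 2.4 (Sample Size) takes its comparator from xenografts ("From literature, this concordance is 0.80 with traditional patient‐derived xenografts") and states: "A sample size of 93 patients will allow us to detect a true value of Cohen's Kappa of 0.95". The remaining inputs to that calculation are given as "with a power of 80% and an allocation of the two groups of 1:1". It makes no allowance for patients who cannot be classed. Section 2.11 says only that the platinum-free interval and platinum sensitivity will be recorded.

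**The concern.** A concordance analysis needs an in vivo class for every patient with an organoid result. The stated rule leaves three groups without one:

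- **Relapse after 6 and up to 12 months.** This falls between the two intervals. The second label suggests that an intermediate, partially sensitive group was meant to be included, yet its only cut-off excludes that range.
- **Progression before 1 month.** The lower bound of the resistant class shuts these patients out.
- **No relapse.** The division applies to relapsed patients only, and a relapse-free patient has no platinum-free interval.

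Two things are at stake. First, membership of the analysis set would depend on the outcome that the organoid is meant to predict. If the gaps were instead closed after organoid and clinical results are known, the choice of rule could move kappa. Second, the sample size counts every enrolled patient, so each unclassed patient costs power.

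**Working it through.** **Inputs from the article.** Kappa 0.80 (comparator) and 0.95 (expected), power 80%, 1:1 split and n = 93 (Section 2.4); two-sided 5% (Section 2.11, not restated for the kappa calculation); class boundaries (Section 2.3). The Abstract gives 43 patients; that is a separate discrepancy, and 93 is used here.

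**Step 1: reproduce 93.** For a one-sample test of Cohen's kappa with a binary rating and both marginals at 0.5, the Fleiss–Cohen–Everitt variance reduces to (1 − κ²)/n. The standard deviations are √(1 − 0.80²) = 0.6000 and √(1 − 0.95²) = 0.3122.

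n = [(1.960 × 0.6000 + 0.8416 × 0.3122) / 0.15]² = 92.003, rounded up to 93.

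Power at n is Φ[(0.15√n − 1.960 × 0.6000) / 0.3122]. At n = 93 this is 80.7%. The arithmetic of the plan is sound. It presumes 93 patients who each have a class, half of them resistant.

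**Step 2: power as patients lose their class (1:1 kept).**

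| Unclassed share of 93 | Classifiable | Power | Enrolment needed for 93 classifiable |
|---|---|---|---|
| 0% | 93 | 81% | 93 |
| 10% | 84 | 74% | 104 |
| 20% | 74 | 64% | 117 |
| 30% | 65 | 54% | 133 |
| 40% | 56 | 43% | 155 |
| 50% | 46 | 31% | 186 |

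**Step 3: an illustration of the unclassed share.** The article gives no distribution of the platinum-free interval, so these inputs are assumptions: exponential, S(t) = exp(−ln 2 × t / median), median 12 or 18 months, 31 months observed after last platinum.

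| Group | Median 12 | Median 18 |
|---|---|---|
| Before 1 month (no class) | 5.6% | 3.8% |
| 1–6 months (resistant) | 23.7% | 16.9% |
| 6–12 months (no class) | 20.7% | 16.4% |
| 12–31 months (second class) | 33.3% | 32.7% |
| No relapse by 31 months (no class) | 16.7% | 30.3% |
| Classifiable | 57.0% = 53 of 93 | 49.5% = 46 of 93 |
| Power at 1:1 | 39% | 31% |

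With medians of 6–24 months and 18–30 months of observation, the classifiable share runs from 24% to 61% (23–57 of 93).

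**Step 4: what happens if the classes are made exhaustive.** Suppose the resistant class takes in everything up to 6 months. Its share in the same illustration is 5.6 + 23.7 = 29.3% or 3.8 + 16.9 = 20.7%, not 50%. With all 93 classified, the general form of the same variance (equal marginals p) gives:

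| Resistant share | SD at κ = 0.80 | SD at κ = 0.95 | Power at 93 |
|---|---|---|---|
| 0.5 | 0.600 | 0.312 | 81% |
| 0.3 | 0.658 | 0.341 | 68% |
| 0.2 | 0.759 | 0.392 | 46% |

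Closing the gaps brings patients back but does not restore the 1:1 split that Section 2.4 assumes.

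**The case against.** The strongest reply is that nothing in the article says unclassed patients are excluded. It is a condensed text, the analysis plan is not shown, and handling of censored patients is often settled there. The label of the second class suggests that the 6–12 month gap is a slip of drafting. Relapse-free patients may silently count as sensitive.

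Part of this stands: exclusion is inferred from an agreement rule that covers only two classes. But the boundaries are stated in the article, and as stated they conflict with their label. Even if relapse-free patients are taken as sensitive, the other two gaps leave 26.3% (5.6 + 20.7) or 20.2% (3.8 + 16.4) unclassed in the illustration. That is about 69 or 74 classifiable patients, with power of about 59% or 64% at 1:1.

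Some stronger readings are tempting but not supported:

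- **That kappa is inflated.** Dropping intermediate relapses could raise it; dropping very early progressors and relapse-free patients, plausibly the clearest cases, could lower it. The net effect is undetermined.
- **That the most informative patients are lost.** This may fit the two extremes, but not the intermediate group.
- **That most truly sensitive patients are lost.** In the illustration, relapse-free patients are 16.7/(16.7 + 33.3) = 33% or 30.3/(30.3 + 32.7) = 48% of those with an interval above 12 months.
- **That the exploratory single-cell groups overlap.** Section 2.3 contrasts "patients that have responded to platinum therapy and from patients that have relapsed within 18 months", but defines neither response nor the start of the 18 months. An overlap cannot be shown, and the primary endpoint does not use these groups.

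**Conclusion.** The point holds as a defect in a stated primary-endpoint rule. The classes are not exhaustive, one label and its cut-off cannot both be right, and the platinum-free interval has no rule for patients without an event. No other section of the article closes these gaps. Taken at its word, the plan yields no concordance result for some patients and selects the rest on outcome.

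The size is not known from the article. What is firm is that 93 delivers 80% power only if all 93 are classifiable and split 1:1. The loss to about 46–53 patients and 31–39% power is an illustration that depends on the exponential shape (which drives the share before 1 month), the median and the length of observation. The 24–61% range is the fairer statement of the uncertainty. A reader might infer that the sample-size arithmetic is wrong; it is not. The mismatch lies between the population it presumes and the one that the class definitions deliver.

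**What to change.** For the endpoint analysis:

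1. Reconcile the second class label with its cut-off in Section 2.3.
2. State mutually exclusive classes that cover every platinum-treated patient. One way is to close the interval between the two classes, remove the 1-month lower bound, and count as sensitive those who remain relapse-free beyond a stated minimum follow-up after the last platinum dose. Only patients censored before that minimum would stay unclassified, and their number should be reported.
3. Add a sensitivity analysis that leaves out the 6–12 month stratum, to show how far agreement depends on intermediate cases.
4. Restate the power in Section 2.4 for classifiable patients at a realistic resistant share, with the share and its basis given.

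This concerns how outcomes are classed for analysis, not how patients are treated. It draws on the follow-up already planned in Section 2.1. The cost is wording, one extra analysis and a less favourable stated power: about 68% at a 30% resistant share and 46% at 20%, even with all 93 classified. If 80% is to be kept, enrolment must be reconsidered.

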### Sample Size

2.4

The sample size was calculated in order to evaluate the concordance between in vitro platinum‐based chemotherapy sensitivity and in vivo sensitivity.

From literature, this concordance is 0.80 with traditional patient‐derived xenografts [33]; we expect a concordance of 0.95 using PDOs [34]. A sample size of 93 patients will allow us to detect a true value of Cohen's Kappa of 0.95, with a power of 80% and an allocation of the two groups of 1:1.

Ninety‐three control patients will also be enrolled to compare the number of CD45+ cells at baseline. This sample size will allow estimating an effect size of CD45+ cell number of less than 0.3 between the control and case groups, with an alpha of 5% and power of 80%.

[32, 33].

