Previous scientific studies have contributed to explaining the pathogenesis of OC using cell lines and animal models; however, the new frontier in biomedical research is represented by organoids, three‐dimensional cell culture systems obtained from a tissue fragment that reproduces the fundamental properties of the original tissue in vitro [20, 21, 22]. Cultures of epithelial organoids, which are found to be genetically and phenotypically stable when derived from both healthy and diseased tissues, can provide a valuable model for in vitro study of various pathologies [20]. They have paved the way for new large‐scale experimental techniques for the identification of genetic mutations that may provide specific sensitivities to anticancer drugs, thus enabling the definition of increasingly personalized treatments. Although organoid technology currently has some limitations, which can be attributed to some factors, including a lack of standardized protocols, heterogeneity amongst organoid preparations, and an absence of complexity and full physiological representation, (PDO) [23] have already found numerous applications in regenerative medicine and can be used to advance knowledge in the field of OC [24].

Starting from the patient's biopsy, the purpose of the MICO study (Study of the Role of the Tumor Microenvironment in Ovarian Cancer) is to characterize in detail the composition of the OC TME, focusing on B lymphocytes and mast cells that have been poorly investigated so far. Simultaneously, PDOs will be generated for each patient and will be employed for in vitro assays to evaluate the tumor's resistance to chemotherapy and to PARP inhibitors (PARP‐I). Furthermore, patients experiencing recurrence will be longitudinally followed to monitor changes in the TME composition and the responsiveness of PDOs to in vitro treatment with drugs. The association between the composition of the TME, the reactivity of the PDOs, and the survival rate of the patients will be analyzed in order to identify whether specific subpopulations of tumor‐infiltrating immune cells are predictive factors of the disease outcome. Finally, PDOs will be stored and used in the future for in vitro studies to find possible interactions among tumor cells and immune cells.

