Analyses of immunophenotype will assist physicians in identifying those eligible for targeted pharmacological therapies and/or early immunotherapy. Personalized treatment plans will involve combinations of therapies to target both the tumor and its microenvironment.

TME is not static [39]; it can change over time, affecting the tumor's response to treatment. Personalized medicine involves monitoring these changes and adapting the treatment plan as needed. Understanding and targeting the TME is an essential aspect of tailoring cancer treatment to the individual patient's needs and optimizing treatment outcomes. In the future, the results of our study may have implications for the development of effective immunotherapy of epithelial OC, an immunogenic disease currently resistant to checkpoint inhibitors.

A limit of our study might be the heterogeneity of TME in OC and the small size of peritoneal biopsies. To overcome this, biopsies will be collected by an experienced gynecologic oncology surgeon and will be collected where carcinosis will be most represented. If the results in our study are promising, to increase the number of patients and overcome the possible heterogeneity of OC, we will design a multicenter study to validate the results in different populations.

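### The 80% power for kappa holds only for a 50:50 platinum split with all 93 patients evaluable, and the plan's own classification rule assures neither

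*Protocol article*

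**What the plan says.** Section 2.4 (Sample Size) of the protocol article cites xenograft work for the reference value ("this concordance is 0.80 with traditional" xenografts) and then sets the target: "we expect a concordance of 0.95 using PDOs". It continues: "A sample size of 93 patients will allow us to detect" a kappa of 0.95, "with a power of 80% and an allocation of the two groups of 1:1". The kappa sentence gives no significance level. Section 2.11 supplies a general one: "All statistical tests will use a two‐tailed significance level of 0.05".

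Section 2.3 defines the in vivo side of the comparison: "Relapsed patients will be divided according to response to platinum treatment as resistant" when the platinum-free interval is 1–6 months, and as partially sensitive or sensitive when it exceeds 12 months. No class is stated for patients who do not relapse or for intervals between 6 and 12 months.

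For the in vitro side, the Introduction says that "PDOs will be generated for each patient". The same section names missing standardised protocols and heterogeneity between preparations as limits of organoid technology, and the Discussion lists "the small size of peritoneal biopsies" as a possible limit of this study.

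**The concern.** Kappa needs two ratings per patient: a carboplatin result from the organoid and a platinum class from follow-up. Its precision depends on how many patients have both and on how evenly the two classes are represented. The plan treats the even split as an allocation, as if it could be arranged at entry. Section 2.1 describes a prospective single-centre study with no selection or quota by platinum response, and the class emerges only after surgery, chemotherapy and follow-up.

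The figure of 93 also serves as the number of patients in the study, whereas the formula behind it needs 93 complete pairs. Section 2.3, as written, leaves some enrolled patients without a class.

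Kappa is the primary endpoint, and this calculation is the stated basis for the number of cases. If the real power is well below 80%, a result that fails to exclude 0.80 would say little either way, yet readers could take it as evidence against organoids as a predictive model.

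**Working it through.** **Inputs.** Reference kappa κ0 = 0.80, true kappa κ1 = 0.95, power 80%, split 1:1 and n = 93 come from Section 2.4. Two-sided α = 0.05 comes from Section 2.11. Reading 0.80 as the null value, and the two groups as resistant and sensitive, is an inference that step 1 supports. The resistant share p and the evaluable fraction are not in the document; the values below are assumptions shown as a range.

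**Step 1: reproduce 93.** For two binary ratings with common prevalence p, the large-sample variance term is

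V(κ) = (1−κ)[(1−κ)(1−2κ) + κ(2−κ)/(2p(1−p))]

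and

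n = [(1.960·√V(κ0) + 0.8416·√V(κ1)) / (κ1−κ0)]².

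At p = 0.5, V(κ) reduces to 1−κ². So V(0.80) = 0.36 (root 0.600) and V(0.95) = 0.0975 (root 0.3122). Then n = [(1.176 + 0.263)/0.15]² = 92.003, rounded up to 93. Variants at p = 0.5 do not match: one-sided 69.4, null variance only 125.6, alternative variance only 34.0. The figure is thus correct for a 50:50 split with every patient analysed, and it holds no reserve.

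**Step 2: power with 93 evaluable patients.** Power = Φ[(√n·0.15 − 1.960·√V(0.80)) / √V(0.95)].

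- At p = 0.5: (1.4466 − 1.1760)/0.3122 = 0.867, so power is 80.7%.
- At p = 0.3: V(0.80) = 0.4331 and V(0.95) = 0.1165, so (1.4466 − 1.2899)/0.3413 = 0.459 and power is 67.7%.

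The formula's cut-off is conservative at this size: in simulation its true upper-tail error is about 1.3–1.7% where 2.5% is allowed. The calibrated column therefore takes its critical value from simulation under κ = 0.80.

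| Resistant share (assumed) | Formula power, n = 93 | Calibrated power, n = 93 | Evaluable n for 80% (formula) |
|---|---|---|---|
| 50% | 80.7% | about 85% | 93 |
| 40% | 77.9% | about 84% | 97 |
| 30% | 67.7% | 78–79% | 111 |
| 25% | 58.5% | 73–74% | 125 |
| 20% | 45.8% | 64–65% | 147 |

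**Step 3: fewer evaluable patients.** Losing 20% leaves 0.8 × 93 = 74; losing 30% leaves 0.7 × 93 = 65.

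| Evaluable n | Split | Formula | Calibrated |
|---|---|---|---|
| 74 | 50:50 | 64.3% | 73–76% |
| 65 | 50:50 | 54.3% | 66–68% |
| 65 | 25:75 | 32.9% | 52–56% |

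**Step 4: who enters kappa.** Set against Section 2.4, the rule in Section 2.3 leaves three sets of enrolled patients without a pair: those without relapse, those relapsing between 6 and 12 months, and those without an organoid result. The document gives no size for any of them.

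**The case against.** Much can be said for the plan. The calculation is correct and its 1:1 assumption is stated openly. Every loss of power shown above rests on a share or fraction that the document does not give. The large-sample formula exaggerates the effect of imbalance: with a calibrated critical value, a split as uneven as 30:70 still gives 78–79%, close to the stated 80%. An allowance for failed cultures and losses, and the definition of the analysis set, are often left to a full protocol or analysis plan, and neither is shown. The Discussion also offers mitigation for small biopsies: an experienced surgeon, and sampling where disease is most represented. Patients without relapse may well be meant to count as sensitive.

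Most of this stands, and it limits the claim. A reader might infer that the plan made an arithmetic error, that 80% power is definitely not delivered, that enrolment is consecutive or unselected, or that the missing attrition allowance is itself a fault. The documents support none of these. The figure of 93 is reproduced; the actual rates are unknown; the text says only that the study is prospective; and a condensed article may omit an allowance.

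What the objection does not remove is in the article itself. Section 2.4 describes as an allocation something that cannot be allocated, and Section 2.3 as written gives no class to some of the patients counted. If patients without relapse are meant to be classed, the text must say so, because that changes both the evaluable number and the split.

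**Conclusion.** The 80% power is conditional on a 50:50 split and 93 complete pairs, and the plan's own classification rule secures neither, so it is not assured for 93 enrolled patients. The size depends on assumptions. Losing 20% of patients at a perfect 50:50 split, or a resistant share of about 25% or less with nobody lost, takes power below 80% by both methods. Mild imbalance alone does not matter much. This is a should-fix on a sample-size assumption. The 43 patients mentioned under Strengths and Limitations in the abstract, against 93 here, are a separate inconsistency and play no part in this conclusion.

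**What to change.** In Section 2.4:

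- State that 93 is the number of evaluable patients, meaning those with both an organoid carboplatin result and a platinum class.
- Replace the 1:1 allocation by the expected resistant share, with its basis.
- Restate power, or the expected half-width of the 95% confidence interval for kappa, in a short table over plausible resistant shares (for example 20–50%) and evaluable fractions (for example 60–100%), using an exact or simulated critical value.

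Reconcile this with Section 2.3, so that it is clear how patients without relapse and those with an interval of 6–12 months are handled in the kappa analysis. Which class they receive is for the investigators to settle.

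The cost is a rewording of these two sections and a small calculation. No extra enrolment is needed. The downside is that the stated power will probably look less favourable.
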